## Donor selection criteria:

The blood donor selection will be done by the Regional Blood Transfusion Center with the following criteria:

1. Male or female patients ≤ 65 years
2. Subjects SARS-CoV-2+ tested by PCR+ during their disease
3. Complete resolution of symptoms at least 14 days prior to donation
4. Subjects must have at least one SARS-CoV-2 negative test by PCR from a nasopharyngeal swab, or, if available, a negative SARS-CoV-2 viremia tested by quantitative PCR in blood, before the blood donation.
5. Donors must have HLA typing and KIR typing performed, in order to decide treatment assignment for patients.
6. Subjects must be tested, at least, for the following:

[figure not shown]

* At least IgG, ideally IgG and IgM

** Mandatory for foreign patients, recommended for nationals

Blood donor apheresis will be split into 2 parts, NK cells (CD3-/CD56+) will be selected for Arm 1 and memory T cells (CD45RA-) for Arm 2.

Both blood products will be infused freshly whenever possible. If necessary, the product will be cryopreserved and frozen for future use.

Blood product from one donor can be utilized for more than one patient.

Donors and patients will be HLA tested. If one or more HLA class I match between donor and recipient is present, they will receive memory T cells. If donor and recipient have less than 1 HLA class I match or HLA-KIR mismatch, they will receive NK cells.

See Figure 3.

******Figure 1. Schematic representation of procedure for blood donor obtention**

## Inclusion criteria

Patients eligible for inclusion in this study have to meet all of the following criteria:

- Male or female patients ≤ 80 years of age.
- Patient with diagnosis of COVID-19 infection with laboratory confirmation by reverse-transcription PCR (RT-PCR) of SARS-CoV-2 or other methods used according to each center protocol prior to study entry.
- Onset of symptoms < 12 days prior to administration of study treatment.
- **Phase I criteria:** Patients requiring hospitalization for COVID-19, with **pneumonia** diagnosed with chest radiograph or computed tomography imaging or **lymphopenia** (absolute lymphocyte counts below 1.2 x 10^9^cells /L) **AND** O_2_Sat ≤ 94% on room air at screening, no oxygen requirement or with an oxygen need of **≤ 2.5 lpm** in nasal cannula.
- **Phase II criteria:** Patients requiring hospitalization with **pneumonia** diagnosed with chest radiograph or computed tomography imaging or **lymphopenia** (absolute lymphocyte counts below 1.2 x 10^9^cells /L) **AND** O_2_Sat ≤ 94% on room air at screening, requiring or not oxygen supplementation (nasal cannula, oxygen mask with reservoir, non-invasive ventilation, etc), but **excluding** mechanical ventilation.
- Have a negative pregnancy test documented prior to enrollment (for females of childbearing potential).
- Be willing and able to comply with study procedures.
- Patients with the ability to comprehend and sign the informed consent
- Written informed consent obtained prior to any screening procedures.

## Exclusion criteria

Patients eligible for this study must not meet any of the following criteria:

- Enrolled in another Clinical Trial for COVID19.
- Rapidly progressive disease with anticipated life-expectancy <72 hours.
- Patients requiring mechanical ventilation.
- Patients with multiorgan failure.
- Moderate - severe (grade ≥ 3) organ impairment (liver, kidney), according to criteria from the National Cancer Institute (NCI CTCAE version 5.0).
- Severe and/or uncontrolled concurrent medical disease that in the opinion of the investigator could cause unacceptable safety risks or compromise compliance with the protocol.
- Have a known history of human immunodeficiency virus infection, Hepatitis B or Hepatitis C; testing is not required in the absence of prior documentation or known history.
- Pregnant or nursing (lactating) women, where pregnancy is defined as the state of a female after conception and until the termination of gestation, confirmed by a positive hCG laboratory test.
- Any other condition that, in the opinion if the Investigator, may interfere with the efficacy and/or safety evaluation of the trial.

1. INVESTIGATIONAL PRODUCT, DOSAGE AND MODE OF ADMINISTRATION

In this clinical trial, our group is proposing the use of adoptive cell therapies for the treatment of COVID-19. Most current clinical trials for the treatment of this disease are investigating the safety and efficacy of antiretroviral or anti-inflammatory drugs.

The two cell therapies proposed in the trial (alloreactive NK cells and memory T cells) are both routinely used in the HSCT setting. These cell subsets are obtained by partial purging of T lymphocytes *ex vivo* using magnetic immunoselection techniques from leukoapheresis material. These procedures are routinely performed as standard of care in the best hemato-oncology centers worlwide. The Cell Therapy and Bone Marrow Unit of the Hematology and Hemotherapy Department at *La Paz* University Hospital, has a wide experience in these cell manipulation techniques, due to the outstanding activity of hematopoietic progenitors transplant carried out in the Hospital.

As examples, figure 4 shows the dynamics of transplant activity over the last 10 years in the Pediatric Hemato-Oncology Department and table 1 shows the different types of HSCT based on the selected cell subpopulations.

[figure not shown]

Figure 2: Different types of HSCT performed in the past ten years (Pediatric Hemato-Oncology Department, *La Paz* University Hospital)

Table 1 Number of NK cells and memory T cells infusions in the last two years (Pediatric Hemato-Oncology Department, *La Paz* University Hospital)

[figure not shown]

These cell subtype selection procedures are not drugs. They are not investigational medicinal products, and they are not included in the Advanced Therapy Medicinal Products category from the substantial manipulation point of view. This way, the cell therapies included in this trial are regulated as Human Cells and Tissues, within the Directive 2004/23/CE of the European Parliament and Council of 31 March 2004, related to setting standards of quality and safety for the donation, procurement, testing, processing, preservation, storage and distribution of human tissues and cells.

Overall, we believe that the strategies proposed in this trial can contribute to increasing the available therapeutic options in the current emergency due to the novel SARS-CoV-2 coronavirus. Moreover, the production and administration to patients of these products, is also a routine clinical activity for our healthcare team that has been proven essentially safe.

**Investigational Medicinal Product:** memory T cells and NK cells from donors who have recovered from COVID-19 and are currently disease- free.

**Form of administration:** intravenous

**Administration dose and Schedule:**

1. **Single Ascending Dose Cohorts (Phase I)**

All patients will receive the SoC of each site for COVID19. Additionally, they will receive the investigational treatment.

**Arm A:** If one or more HLA class I match between donor and recipient is present, patients will receive memory T cells.

- Cohort 1: starting dose will be up to 1x10^5^/kg.
- Cohort 2: 1x10^5^/kg to 5x10^5^/kg
- Cohort 3: 5x10^5^/kg to 1x10^6^/kg.

**Arm B:** If donor and recipient have less than one HLA class I match or HLA-KIR mismatch, they will receive NK cells.

- Cohort : starting dose will be up to 1x10^6^/kg
- Cohort 2: 1x10^6^/kg to 5x10^6^/kg.
- Cohort 3: 5x10^6^/kg to 1x10^7^/kg.

The next cohort will open if all the patients in the previous cohort have been included and no safety issues have aroused during the follow-up after cell infusion (data of at least 7 days after cell infusion is required to proceed to each subsequent dose).

Those patients showing clinical improvement at day 7 according to the investigator (based on respiratory status and blood-result tests) who haven’t shown previous toxicities of grade 3 or higher, can receive a second cycle with the same dose at Day 7, if the investigator considers it appropriate.

The 18 patients included in the Phase I will continue to be followed for possible DLTs during the 21 days following cell infusion.

1. **Dose level decisions for Phase II** will be guided by safety and DLT data from Phase I. Phase II will begin once RP2D is established based on Phase I data.

The recommended dose will be the maximum tolerated dose (MTD) unless no MTD is determined in the dose escalation segment of the study. In this situation, the recommended dose will be the highest dose evaluated in the dose escalation segment.

Those patients showing clinical improvement at day 7 according to the investigator (based on respiratory status and blood-result tests) who haven’t shown previous toxicities of grade 3 or higher, can receive a second cycle with the same dose at Day 7, if the investigator considers it appropriate.

Third party donors will be individuals in recovery phase, with no symptoms for at least 14 days and at least one SARS-CoV-2 negative test. The blood donor selection will be done by the Regional Blood Transfusion Center. Refer to "donor selection criteria" in section 5 for further details.

Blood donor apheresis will be split into 2 parts, NK cells (CD3-/CD56+) will be selected for Arm A and T memory cells (CD45RA-) for Arm B.

Blood product from one donor can be utilized for more than one patient.

## Subject Treatment Assignment

Patients will be allocated into two groups: Arm A and Arm B depending on HLA typing.

For the phase I, patients on each arm will subsequently undergo a correlative allocation into the different cohorts (1,2,3).

The decision to proceed to each subsequent dose level (next cohort) will be made based on safety and tolerability data from the prior lower dose level. Safety data for at least 7 days post-dose from all the subjects at the prior lower dose will be reviewed before dose escalation.

The next cohort will open if all the patients in the previous cohort have been included and no safety issues have aroused during the follow-up after cell infusion (data of at least 7 days after cell infusion is required to proceed to each subsequent dose). Patients will continue to be followed for possible DLTs during the 21 days following cell infusion.

For phase II, eligible patients will be allocated to arm A or B considering HLA typing and within each arm they will then be randomized in a 1:1 ratio to 1 of 2 treatment groups (SoC or SoC+RP2D).

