## Study treatment

**Phase I:**

- **Arm A**: patients will receive memory T cells:
- Cohort 1: Starting dose will be up to 1x10^5^/kg
- Cohort 2: 1x10^5^/kg to 5x10^5^/kg
- Cohort 3: 5x10^5^/kg to 1x10^6^/kg
- **Arm B**: patients will receive NK cells:
- Cohort 1: starting dose will be up to 1x10^6^/kg
- Cohort 2: 1x10^6^/kg to 5x10^6^/kg
- Cohort 3: 5x10^6^/kg to 1x10^7^/kg

The next cohort will open if all the patients in the previous cohort have been included and no safety issues have aroused during the follow-up after cell infusion (data of at least 7 days after cell infusion is required to proceed to each subsequent dose).

Those patients showing clinical improvement at day 7 according to the investigator (based on respiratory status and blood-test results), who haven’t shown previous toxicities of grade 3 or higher **and** if donor chimerism doesn´t persist, can receive a second cycle with the same dose at Day 7, if the investigator considers it appropriate.

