**Phase I:**

Patients with SARS-CoV-2+ pneumonia or lymphopenia **and** O_2_Sat ≤ 94% on room air at screening, with no oxygen requirement or with an oxygen need of **≤ 2.5 lpm** in nasal cannula, will be selected.

This phase has a single ascending dose design with up to 3 planned dose levels:

- **Arm A:** patients will receive memory T cells:
  - Cohort 1: Starting dose will be up to 1x10^5^/kg
  - Cohort 2: 1x10^5^/kg to 5x10^5^/kg
  - Cohort 3: 5x10^5^/kg to 1x10^6^/kg
- **Arm B:** patients will receive NK cells:
  - Cohort 1: starting dose will be up to 1x10^6^/kg
  - Cohort 2: 1x10^6^/kg to 5x10^6^/kg
  - Cohort 3: 5x10^6^/kg to 1x10^7^/kg

Additionally to the investigational product, all patients will receive the local standard of care for COVID-19 treatment.

The next cohort will open if all the patients in the previous cohort have been included and no safety issues have aroused during the follow-up after cell infusion (data of at least 7 days after cell infusion is required to proceed to each subsequent dose).

Those patients showing clinical improvement at day 7 according to the investigator (based on respiratory status and blood-test results) who haven’t shown previous toxicities of grade 3 or higher, can receive a second cycle with the same dose at Day 7, if the investigator considers it appropriate.

The 18 patients in the Phase I will continue to be followed for possible DLTs during the 21 days following cell infusion.

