**Phase II**

- To determine the efficacy of a single infusion of NK or memory T cells from a healthy donor recovered from COVID-19.

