## Other complications that are unforeseeable may also occur. The most serious complications usually occur within the first month after T cell or NK cell infusion.

1. STUDY POPULATION

The target population for enrolment in the study will be patients with pneumonia or lymphopenia related to COVID-19.

- Pneumonia will be diagnosed as an acute respiratory disorder characterized by the presence of cough and at least one of the following: new-onset focal chest signs, fever for more than 4 days or dyspnea/tachypnea.
- Lymphopenia will be defined as lymphocyte counts below 1.2×10⁹.

A total of 182 patients will be included in this clinical trial. The plan is to enroll 18 patients in the first dose escalation segment (phase I): 9 patients per arm (3 patients in each cohort for both arms).

A total of 164 patients will be included in the phase II: 82 patients per arm.

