1. STUDY OUTCOME MEASURES

## Primary outcome:

**Phase I**

The primary outcomes of the Phase I in this study are:

- The primary outcome will be the occurrence of DLTs in all patients during the study treatment, until 21 days after cell infusion, and the MTD.

DLT is defined as:

- - any grade 3 or higher toxicity with an attribution of definitely or probably related to the infusion of the cells and
  - any lower grade toxicity that increases to a grade 3 or higher as a direct result of the cell infusion.

Based on this, **RP2D** will be defined as: The recommended dose will be the MTD unless no MTD is determined in the dose escalation segment of the study. In the latter, the recommended dose will be the highest dose evaluated in the dose escalation segment.

- Incidence and nature of DLT of a single infusion of NK or memory T cells from a healthy donor recovered from COVID-19 (dose escalation).

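### Dose rules that need reconciling: the second-cycle condition differs between sections, the RP2D rests on an undefined MTD, and a Day 7 second infusion falls inside the DLT window of a single-infusion objective

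*Protocol*

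**What the plan says.** **Second cycle.** In the Protocol summary, *Study treatment*, the Phase I text makes re-treatment conditional: "if donor chimerism doesn´t persist, can receive a second cycle with the same dose at Day 7". The footnotes to Tables 2 and 3 carry the same condition. The Phase II text of that summary section, both phases under *Study design* (Study Approach), and *Administration dose and Schedule* leave it out. There, an improving patient without earlier toxicity of grade 3 or higher "can receive a second cycle with the same dose at Day 7, if the investigator considers it appropriate".

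**RP2D.** *Administration dose and Schedule* and *Primary outcome* (Phase I) set the RP2D to the MTD. If none is determined, the first of these adds: "In this situation, the recommended dose will be the highest dose evaluated in the dose escalation segment".

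**Escalation.** *Subject Treatment Assignment* states: "Safety data for at least 7 days post-dose from all the subjects at the prior lower dose will be reviewed before dose escalation". Besides full enrolment of the cohort before it, moving up a level depends on the finding that "no safety issues have aroused during the follow-up after cell infusion (data of at least 7 days after cell infusion is required"). The same section then continues DLT follow-up to Day 21.

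**DLT outcome.** The Phase I primary outcome is the "occurrence of DLTs in all patients during the study treatment, until 21 days after cell infusion, and the MTD".

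**Objectives.** Under *Trial Objectives*, the Phase I objective and the DLT and safety objectives concern one infusion, as does the DLT incidence listed under *Primary outcome*. The Phase II objective is "To determine the efficacy of a single infusion of NK or memory T cells from a healthy donor recovered from COVID-19".

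**Risk.** The section on risks to recipients ends: "The most serious complications usually occur within the first month after T cell or NK cell infusion".

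**The concern.** Phase I exists to deliver one dose per product to Phase II. For that, a reader must be able to tell who may be re-infused, which infusion a toxicity belongs to, and what dose results when escalation stops.

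- Sites that follow different sections would re-treat different patients. The proportion receiving a second cycle is itself a listed secondary outcome.
- The RP2D rule depends on a term that the Protocol does not define. Its fallback does not exclude a dose at which a safety issue stopped escalation.
- For a re-treated patient, a DLT after Day 7 cannot be assigned to one infusion, although the objective is about one infusion. In Phase II the second infusion also precedes the Day 14 recovery endpoint, so that endpoint reflects one or two infusions.
- A cohort can be judged clean on part of the DLT window, and the text is silent on a DLT that appears later.

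**Working it through.** **The plan's own figure.** Phase I size: 3 patients × 3 cohorts × 2 arms = 18, as stated. 18 + 164 = 182, also as stated.

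**1. Second-cycle condition, side by side**

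| Place in the Protocol | Chimerism must have gone? |
|---|---|
| Summary, *Study treatment*, Phase I | Yes |
| Summary, *Study treatment*, Phase II | Not mentioned |
| *Study design*, Phase I | Not mentioned |
| *Study design*, Phase II | Not mentioned |
| *Administration dose and Schedule*, both phases | Not mentioned |
| Table 2 footnote (Phase I) | Yes |
| Table 3 footnote (Phase II) | Yes |

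The conflict runs within each phase, so it is not a difference between Phase I and Phase II. The documents give no frequency of persistent chimerism, so the number of patients affected cannot be computed.

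**2. What the RP2D rule returns.** No section defines the MTD, gives a DLT count that stops escalation, or says what counts as a safety issue.

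- All three cohorts completed without a stop: the default gives the cohort 3 dose. This is clear.
- Stop at cohort 2 or 3: if the MTD is taken by convention as the level below, that level is the RP2D. If no MTD is declared, the highest dose evaluated is the one that stopped escalation. The text does not choose between these.
- Stop at cohort 1: there is no lower planned level to name, so the default points to the cohort 1 dose itself.

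A stop is not remote. P(at least one DLT among 3) = 1 − (1 − q)³, where q is the chance of a DLT by Day 21 (assumed; not in the documents). For q = 0.10, 0.20 and 0.33 this is 0.27, 0.49 and 0.70.

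Exposure in Phase II: 164 / 2 arms = 82 per arm. Randomised 1:1, 82 / 2 = 41 are infused with each product.

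**3. Second infusion and the DLT window.** Day 7 lies inside Days 0 to 21. Counted from the first infusion, the window ends on Day 21 and leaves 21 − 7 = 14 days after the second. Counted from the second, it ends on Day 7 + 21 = 28. The text does not say which applies. At the 7-day minimum, the escalation review can fall on the day of the second infusion and so need contain no follow-up after it.

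Two equal cycles double the cumulative dose (upper limits, cells/kg):

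| Cohort | Arm A: 2 × limit | Arm B: 2 × limit | Compared with planned single doses |
|---|---|---|---|
| 1 | 2×10⁵ | 2×10⁶ | inside cohort 2's range |
| 2 | 1×10⁶ | 1×10⁷ | equals cohort 3's upper limit |
| 3 | 2×10⁶ | 2×10⁷ | above every planned level |

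**4. Seven-day review against the 21-day outcome (lesser point).** The minimum covers 7/21 = one third of the window. Let f be the share of DLTs with onset by Day 7 (assumed). If all three patients are seen for exactly 7 days, P(no DLT seen) = (1 − q·f)³; at Day 21 it is (1 − q)³.

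| q | f = 1/3 | f = 1/2 | f = 3/4 | f = 1 (same as Day 21) |
|---|---|---|---|---|
| 0.20 | 0.81 | 0.73 | 0.61 | 0.51 |
| 0.33 | 0.71 | 0.58 | 0.43 | 0.30 |
| 0.50 | 0.58 | 0.42 | 0.24 | 0.125 |

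Example: q = 0.33, f = 1/3 gives (1 − 0.11)³ = 0.89³ = 0.705, against 0.67³ = 0.301. The difference, 0.404, is the chance that a cohort looks clean at review and has a DLT by Day 21. At f = 3/4 it is 0.426 − 0.301 = 0.125; at f = 1 it is zero.

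Exactly 7 days for all three is the extreme case. If the three have 7, 14 and 21 days with uniform onset, P(none seen) = 0.89 × 0.78 × 0.67 = 0.465, a gap of 0.16.

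**The case against.** **The two windows are stated openly.** *Study design*, *Administration dose and Schedule* and *Subject Treatment Assignment* each give the 7-day minimum together with DLT follow-up to Day 21. That reads as a deliberate staggered rule, and 7 days is only a floor. This stands: the two windows do not contradict each other. What remains is that no section says how a DLT on Days 8 to 21 bears on a cohort already open.

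**The Phase II dose does not rest on 7-day data.** A reader might infer that it does. The documents do not support this: the Phase I outcome runs to Day 21 in all patients, all 18 are followed for that time, and Phase II starts only once the RP2D is established from Phase I data. The 7-day minimum governs cohort opening only.

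**Convention fills the MTD gap.** Under the usual reading, a stop at cohort 2 or 3 makes the level below the MTD, and dose decisions are said to be guided by safety and DLT data. This softens the point: the rule can return the stopping dose, but need not. It does not settle a stop at cohort 1, and the Protocol never adopts the convention.

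**The second cycle is optional** and barred after toxicity of grade 3 or higher. So the attribution problem concerns re-treated patients only, not every DLT after Day 7.

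**The size of the 7-day gap is fragile.** A gap of about 40 percentage points needs uniform onset and exactly 7 days on all three patients. The documents give no onset times. The remark about the first month does not show that DLTs arise after Day 7, and a safety issue other than a DLT could also halt escalation.

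**Conclusion.** Three defects hold on the text alone: the contradictory chimerism condition, an RP2D rule that rests on an undefined MTD, and the mismatch between single-infusion objectives and a Day 7 second infusion inside the DLT window. None depends on an assumed rate. The second could bring a stopping dose to about 41 infused Phase II patients per product. A figure of 82 is tempting, but it would require both products' rules to fail together.

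The 7-day review is a lesser point, an omission about late DLTs. At an assumed 33% DLT rate and exactly 7 days on each of three patients, the chance that a cohort looks clean but has a DLT by Day 21 runs from 0.40 (one third of onsets by Day 7) through 0.13 (three quarters) to zero (all).

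**What to change.** By protocol amendment:

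1. Reconcile the chimerism condition across the summary *Study treatment* (both phases), *Study design* (both phases), *Administration dose and Schedule*, and the footnotes to Tables 2 and 3.
2. Define the MTD, and limit the highest-dose default so that the RP2D rule has a stated result when escalation stops for safety at cohort 1, 2 or 3.
3. Reconcile the single-infusion wording in *Trial Objectives* and *Primary outcome* with the Day 7 second cycle. State from which infusion the DLT window runs, and tabulate DLTs separately after the first and second infusion.
4. Reconcile *Study design*, *Administration dose and Schedule* and *Subject Treatment Assignment* with *Primary outcome* on how DLTs on Days 8 to 21 bear on a cohort already open.

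Which clinical rule applies in each case is for the sponsor to decide. The cost is an amendment with ethics committee approval; clarifying the text needs no change to the sample size. Calendar time is affected only if the sponsor chooses a longer review before escalation, by up to 21 − 7 = 14 days per step.
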